## Abstract

Cognitive impairment, defined as a decline in memory and executive function, is one of the most severe complications of traumatic brain injury (TBI). Patients with TBI are often unable to return to work due to cognitive impairment and their overall quality of life is reduced. TBI can bring a serious economic burden to patient's families and to society. Reported findings on the efficacy of repetitive transcranial magnetic stimulation (rTMS) in improving cognitive impairment following TBI are inconsistent. The purpose of the proposed study is to investigate whether rTMS can improve memory and executive function in patients with TBI. Herein, we propose a prospective randomized placebo-controlled (rTMS, sham rTMS, cognitive training), parallel-group, single-center trial. 36 participants with a TBI occurring at least 6 months prior will be recruited from an inpatient rehabilitation center. Participants will be randomly assigned to the real rTMS, sham rTMS, or cognitive training groups with a ratio of 1:1:1. A 20-session transcranial magnetic stimulation protocol will be applied to the left and right dorsolateral prefrontal cortices (DLPFC) at frequencies of 10 Hz and 1 Hz, respectively. Neuropsychological assessments will be performed at four time points: baseline, after the 10th rTMS session, after the 20th rTMS session, and 30 days post-intervention. The primary outcome is change in executive function assessed using the Shape Trail Test (STT). The secondary outcome measures are measures from neuropsychological tests: the Hopkins Verbal Learning Test (HVLT), the Brief Visuospatial Memory Test (BVMT), the Digit Span Test (DST). We report on positive preliminary results in terms of improving memory and executive function as well as beneficial changes in brain connectivity among TBI patients undergoing rTMS and hypothesize that we will obtain similar results in the proposed study.

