### Sample Size Estimation

Sample size calculations were based on non-inferiority tests, as the purpose of this study was to show that the rTMS intervention was not inferior to cognitive training. According to studies showing that the effect size of working memory training on MCI is 0.74 and executive function is 0.575, we calculated the sample size using PASS 15 (effect size is 0.7, α is 0.05, power is 0.9). sample sizes of *n* = 10, *n* = 10, and *n* = 10 are obtained for the three groups. Moreover, two additional patients will be added to each group to compensate for possible dropouts. A total of 12 patients will be allocated to each group.

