### Outcome Measures

The primary outcome of the proposed study is current executive functioning as measured by the Shape Trail Test (STT), which was revised for the Chinese-speaking population based on the Trail Making Test (TMT). The secondary outcome measures are neuropsychological test findings based on the Hopkins Verbal Learning Test (HVLT), the Brief Visuospatial Memory Test (BVMT), and the Digit Span Test (DST), as well as evaluations of the safety and tolerability of rTMS in patients with TBI.

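### The sample size is planned on an effect of 0.7, unexplained and above the 0.575 that the same sentence gives for executive function, the primary domain; the stated 90% power is therefore not supported for the primary outcome

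*Protocol article*

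**What the plan says.** All references are to the Protocol article.

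- **Sample Size Estimation** gives two figures from studies of training in mild cognitive impairment (MCI): "the effect size of working memory training on MCI is 0.74 and executive function is 0.575, we calculated the sample size using PASS 15". The inputs that follow are: "effect size is 0.7, α is 0.05, power is 0.9". The result is: "sample sizes of *n* = 10, *n* = 10, and *n* = 10 are obtained for the three groups". For dropout, "two additional patients will be added to each group to compensate for possible dropouts", which makes 12 per group and 36 in all.
- The same section names the framework: "Sample size calculations were based on non-inferiority tests". It gives no margin, does not say which effect-size metric 0.7 is in, and does not explain how 0.7 was chosen.
- **Abstract**: "The primary outcome is change in executive function assessed using the Shape Trail Test (STT".
- **Outcome Measures**: "The primary outcome of the proposed study is current executive functioning as measured by the Shape Trail Test (STT". The two memory tests and the Digit Span Test (DST) are secondary there.
- **Table 1** places the DST beside the STT in the primary row, with both labelled as executive function.

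**The concern.** A planning effect should belong to the outcome the trial is sized for. The section prints one figure for executive function and one for working memory. It then uses a value 0.04 below the working-memory figure and 0.125 above the executive-function figure. A larger assumed effect yields a smaller sample or a higher stated power, so the choice flatters the calculation, and the text does not defend it.

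At stake is how the STT result will be read. With 90% power on paper, a null result looks like a well-powered negative. On the plan's own executive-function figure, that reading is not earned.

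**Working it through.** **Inputs.** Effect 0.7, alpha 0.05, power 0.9, 10 per group, 12 with the dropout allowance, cited effects 0.74 and 0.575 (Sample Size Estimation); three groups in equal allocation (Study Design). The metric and the sidedness are not stated.

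**1. Reproduce the printed 10.** One-way ANOVA, k = 3 groups, noncentral F with 2 and 3(n − 1) degrees of freedom and noncentrality λ = 3n·f².
- f = 0.7, n = 9: λ = 27 × 0.49 = 13.23, critical F 3.403, power 0.873.
- f = 0.7, n = 10: λ = 30 × 0.49 = 14.70, critical F 3.354, power 0.911.

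Ten is the smallest n that reaches 0.9, as printed.

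**2. Same routine with 0.575** (f² = 0.3306).

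| n per group | λ | power |
|---|---|---|
| 10 | 9.92 | 0.764 |
| 12 | 11.90 | 0.848 |
| 13 | 12.89 | 0.879 |
| 14 | 13.89 | 0.904 |

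The ratio of planning values is 0.7/0.575 = 1.22. Twelve evaluable per group is the best case, because the Statistical Analysis section restricts the analysis to completers.

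**3. Is 0.7 an average of the two figures?** (0.74 + 0.575)/2 = 0.6575. At n = 10 this gives 0.871, and 11 per group would be needed. So it is not.

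**4. Figures read as standardized mean differences between two arms.** t-test, 10 per arm, noncentrality d·√(n/2).
- d = 0.7: 0.7 × √5 = 1.565; power 0.317 two-sided, 0.445 one-sided. Reaching 90% takes 44 or 36 per arm, so this reading does not reproduce 10.
- d = 0.575: 0.575 × √5 = 1.286; power 0.230 two-sided, 0.342 one-sided. Reaching 90% takes 65 or 53 per arm.

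**5. The framework the text names.** Non-inferiority with a margin of 0.7 SD and no true difference, n = 2(z₁₋α + z₀.₉)²/0.7²:
- one-sided 0.05: 2 × (1.645 + 1.282)²/0.49, giving 35 per arm;
- one-sided 0.025: 43 per arm.

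Ten per arm appears only if a true advantage of 0.7 SD is added to a margin of 0.7 SD, 1.4 SD in all. On a one-sided 0.05 t-test this gives 0.884 at n = 9 and 0.914 at n = 10. The text states neither a margin nor a true advantage. Putting 0.575 in both places, purely as a like-for-like check, gives 0.796 at 10, 0.861 at 12, and 14 per arm for 90%.

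**6. Repeated measures.** Between-group test over 4 time points, λ = 3n·f²·4/(1 + 3ρ), with ρ assumed because the document gives none.
- ρ = 0.5: 0.7 needs only 7 per group (0.925), not 10; 0.575 at n = 10 gives 0.931.
- 0.575 at n = 10 for other ρ: 0.958 (ρ = 0.4), 0.900 (0.6), 0.866 (0.7), 0.832 (0.8).
- ρ = 0.9: 0.7 does return 10 (0.898 at n = 9, 0.931 at n = 10); 0.575 at n = 10 then gives 0.797.

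So each routine found that turns 0.7 into 10 per group gives 76% to 80% when 0.575 replaces it.

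**The case against.** **The clause is ambiguous and the cited studies are not shown.** Working memory training can name an intervention, so 0.575 might be the effect of executive-function training and not the effect on an executive outcome. Either way the figures come from training in MCI, not from rTMS in TBI or from the STT. This stands as a caution. It does not explain 0.7, and 0.575 remains the only figure in the document attached to executive function.

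**The primary row of Table 1 includes the DST**, and the DST section scores it as a memory span. That might argue for a value between the two figures. But Table 1 labels both tests as executive function, the Abstract and Outcome Measures name the STT alone as primary, and no compromise is described.

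**The ANOVA is inferred.** This stands. The text speaks of non-inferiority, and other routines reach 10 under assumptions that the document does not state.

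**A reader might infer that power is overstated on every reading.** The documents do not support that. A repeated-measures test with correlation up to about 0.6 would have at least about 90% power at f = 0.575 and n = 10. The section describes no such calculation, and at those correlations it would not return 10 from 0.7.

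**A reader might also conclude that the trial simply has 76% power.** That holds only if 0.575 is Cohen's f. With three groups, f = 0.575 implies a largest between-group difference of 0.575 × 3/√2 = 1.22 SD if one group differs, or 0.575 × √6 = 1.41 SD if the means are evenly spaced. If 0.575 is itself a mean difference in SD units, 76% is far too high.

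**Conclusion.** The point holds. The planning effect is unexplained, lies above the document's own figure for the primary domain, and is not the average of the two figures cited. The stated 90% is therefore unsupported for the STT. In the one-way ANOVA that reproduces the printed sample size, power on 0.575 is 76% at 10 per group (91.1 − 76.4 = 14.7 points below the reproduced value) and 85% if all 12 are evaluable.

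This rests on three assumptions: that 0.575 is the figure for an executive-function outcome, that it is Cohen's f, and that the test is a one-way ANOVA. The document confirms none of them. Under a two-arm mean-difference reading, power is about 23% to 34% at 10 per arm. The missing margin, and the conflict between non-inferiority here and the superiority hypothesis in the Introduction, are separate issues.

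**What to change.** Keep 36 patients and rewrite the sample-size sentence so that it:

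1. bases the planning effect for the STT on the executive-function figure (0.575), or gives a reason for another value;
2. names the test and the effect-size metric;
3. restates the power for that test. About 76% with 10 evaluable per group (85% with 12) may be printed only if 0.575 is Cohen's f in a three-group one-way ANOVA. If it is a standardized mean difference between two arms, the figures at 10 per arm are about 23% two-sided or 34% one-sided.

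Do not use 0.575 as a non-inferiority margin: a margin equal to the full training effect would preserve none of the comparator's benefit. If non-inferiority is kept, the margin needs its own justification.

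The cost is a rewritten sentence and a less favourable stated power, with no added patients, visits or procedures.

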## Materials and Methods

### Study Design

The study is a prospective randomized placebo controlled, parallel-group trial that will be conducted at the Affiliated Hospital and the Second Clinical Medical College of North Sichuan Medical University. The protocol has been registered with the China Clinical Trial Registry (item number: ChiCTR2100050753). Our study will show improvement in cognitive function in patients with TBI following rTMS bilateral DLPFC intervention. The findings may provide a rationale for an approach of rTMS intervention for cognitive function in patients with TBI. Thirty-six patients with TBI will be enrolled in the trial. The physicians will provide patients with detailed information about the trial in verbal and written form before the trial begins.All patients will voluntarily sign an informed consent form. All patients will be screened according to eligibility criteria. 36 subjects will be randomized in a 1:1:1 ratio into the real-rTMS group, the Cognitive training group and the sham-rTMS group. All subjects will be required to perform neuropsychological assessments at before intervention, post-10 sessions, post-20 sessions, and 30 days after the intervention. MRI will be performed at pre-intervention and post-20 sessions. All patients will receive intervention for 4 weeks (30 minutes per day, 5 days per week). The diagram and schedule for the study are shown in Figure 1 and Table 1.

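### The claimed 90% power with 10 patients per group does not follow from the non-inferiority framework and effect size of 0.7 that the article states

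*Protocol article*

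**What the plan says.** The Sample Size Estimation section names the framework: "Sample size calculations were based on non-inferiority tests", the comparison being rTMS against cognitive training. It takes its effect size from "studies showing that the effect size of working memory training on MCI is 0.74 and executive function is 0.575", and gives the inputs as follows: "we calculated the sample size using PASS 15 (effect size is 0.7, α is 0.05, power is 0.9". Sizes of 10, 10 and 10 "are obtained for the three groups", and then "two additional patients will be added to each group to compensate for possible dropouts", which makes 12. The Study Design section agrees on the total: "36 subjects will be randomized in a 1:1:1 ratio".

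The section does not say which metric 0.7, 0.74 and 0.575 are on, which PASS procedure was run, whether alpha is one- or two-sided, or what the non-inferiority margin is.

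Three other places bear on the number:
- The Introduction hypothesizes that rTMS is superior to both sham and cognitive training.
- The Statistical Analysis section plans ANOVA with Bonferroni post hoc comparisons, or Kruskal-Wallis, and restricts the analysis to completers.
- The Abstract and Outcome Measures sections make executive function (Shape Trail Test) the primary outcome.

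**The concern.** Ten per group is very small for 90% power at an effect size of 0.7, if that is a difference between two means in SD units. Non-inferiority sizing with a margin of that order does not give so small a number either, unless a sizeable true advantage is also assumed. The likely explanation is a mix of scales: a treatment effect in SD units entered where the software expected Cohen's f, which for three groups is a much larger effect at the same numerical value.

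At stake is the credibility of the trial's main comparison. A reader who trusts the 90% would take a non-significant result as good evidence that the assumed effect is absent. With real power nearer one in three, such a result would be the expected one even if the effect were present.

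**Working it through.** **Inputs (Sample Size Estimation):** effect size 0.7; cited effects 0.74 and 0.575; alpha 0.05; power 0.9; 10 per group before dropout. **Assumptions:** 0.7, 0.74 and 0.575 are standardized mean differences d; sidedness is unstated, so both are shown.

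**1. Reproducing the figure of 10.** Three-group one-way ANOVA, f = 0.7, noncentral F with noncentrality N·f²:
- 10 per group: 30 × 0.49 = 14.7 on 2 and 27 df, power 0.911.
- 9 per group: power 0.873.

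So 10 is exactly the smallest adequate size. One other route also gives 10: non-inferiority with a 0.7 SD margin plus a 0.7 SD true advantage, one-sided 0.05. The noncentrality is (0.7 + 0.7) × √(10/2) = 3.13, and power is 0.914.

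**2. What those routes assume.** For group means (0, 0, d), f = d√2/3. For evenly spaced means, f = d/√6. Setting f = 0.7:
- one group differs: d = 0.7 × 3/√2 = 1.48 SD;
- third group midway: d = 0.7 × √6 = 1.71 SD.

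The non-inferiority route uses 0.7 + 0.7 = 1.4 SD in total. Against the cited effects, 1.4/0.74 = 1.9 and 1.71/0.575 = 3.0, so these routes need roughly two to three times what the sources report.

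**3. Size needed if 0.7 is a mean difference.** Normal approximation n = 2(z_α + z_β)²/d²:
- Two-sided 0.05: 2 × (1.960 + 1.282)²/0.49 = 42.9, so 43; exact t gives 44.
- One-sided 0.05, which is also non-inferiority with a 0.7 SD margin and true difference 0: 2 × (1.645 + 1.282)²/0.49 = 35.0; exact t gives 36.
- Bonferroni over three pairs, two-sided: 57 (exact t).
- Two-sided at d = 0.575: 2 × (1.960 + 1.282)²/0.3306 = 63.6, so 64; exact t gives 65.

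**4. Power with the planned number.** Two per group are expected to drop out and only completers are analysed, so 10 per group is the planned evaluable number. Noncentral t on 18 df, noncentrality d√(10/2): 1.565 at d = 0.7 and 1.286 at d = 0.575.

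| Test, 10 per group | d = 0.7 | d = 0.575 |
|---|---|---|
| t, two-sided 0.05 | 0.32 | 0.23 |
| t, one-sided 0.05 | 0.44 | 0.34 |
| t, Bonferroni (0.05/3, two-sided) | 0.17 | 0.11 |
| ANOVA, f = d/√6 to d√2/3 | 0.24 to 0.31 | 0.18 to 0.22 |

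For d = 0.7 the ANOVA f runs from 0.286 to 0.330. If nobody drops out (12 per group), two-sided power is 0.37 at 0.7 and 0.27 at 0.575. The most favourable combination of the cited effects (0.74, one-sided, 12 per group) gives 0.54.

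**5. Effect detectable with 90% power**, two-sided t: 1.53 SD with 10 per group, 1.39 SD with 12.

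**The case against.** The strongest reply is that the metric is unstated. If 0.7 is Cohen's f and the cited 0.74 and 0.575 are on that scale too, the arithmetic is right and what remains is an optimistic assumption. That stands as a condition on every power figure here. It does not rescue the paragraph, because a three-group F test is not the non-inferiority test the section says it used.

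A reader might infer that the sponsor certainly ran an ANOVA with f = 0.7, or that nothing else produces 10. The article supports neither. It names no procedure, and the margin-plus-advantage route also gives 10 within the non-inferiority framework it does name. ANOVA is the likelier source: it yields three equal group sizes in one calculation and matches the planned analysis. That is still inference. The section states neither a margin nor an assumed advantage, so the second route is not documented either.

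It is also tempting to quote one figure for the real power. No single figure holds: it runs from 0.17 to 0.44 at d = 0.7 with 10 per group, depending on the test. Baseline adjustment would raise it, but at 10 per group and d = 0.7 a baseline correlation of 0.8 brings two-sided power only to 0.69. It takes about 0.9 to pass 90% (0.92), and no adjustment is described.

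The article condenses a fuller protocol, which may hold the margin, sidedness and procedure. Their absence alone is therefore not the point. The point is that the inputs and result that are printed do not fit the framework and sources printed beside them.

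Three lesser criticisms do not add to the case. The value 0.7 lies between the two cited effects, so choosing it is not an arithmetic error. Borrowing from training in mild cognitive impairment is a weak justification rather than a miscalculation. And nothing in the article says that the sponsor would read a null result as non-inferiority; that is a risk to guard against.

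**Conclusion.** The power statement is wrong as written and must be corrected. Under the stated framework, with a 0.7 SD margin and no true difference, 36 per group are needed rather than 10; a two-sided comparison at 0.7 needs 44. With 10 evaluable per group, two-sided power is about 0.32 at d = 0.7 and 0.23 at 0.575, the value quoted for the domain of the primary outcome.

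These figures assume that the cited effects are standardized mean differences and that analyses are unadjusted. None of the calculations that treat the cited values as mean differences reaches 0.9 for an effect of that size without either a further assumed advantage that the section does not state or a baseline adjustment that the article does not describe. Which calculation the sponsor actually ran remains unknown.

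Separately, sizing for non-inferiority conflicts with a superiority hypothesis and an analysis made up of difference tests. Only the sponsor can settle which is intended.

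**What to change.** Keep 36 patients and rewrite the paragraph:

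1. State the test, the effect-size metric, the sidedness and any margin and assumed true difference actually used.
2. Replace the stated power of 0.9 with the power at 10 evaluable per group. On the mean-difference reading this is about 32% for 0.7 and 23% for 0.575 (two-sided 0.05). Add that 90% power holds only for a difference of about 1.5 SD. If the metric or test proves to be different, recompute on that basis.
3. Reconcile the non-inferiority wording with the hypothesis in the Introduction and the tests in the Statistical Analysis section. If non-inferiority is kept, it needs a margin and a matching test.
4. Report between-group effect estimates with 95% confidence intervals, so that a non-significant difference is not taken as non-inferiority.

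The cost is one rewritten paragraph, consistent wording elsewhere and a much less favourable stated power. No extra patients or visits are needed.

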### Randomization

A computer-generated list of random numbers will be placed in an order-numbered, non-transparent, sealed envelope, and participants will be randomly assigned to real rTMS, sham rTMS, and cognitive training groups in a 1:1:1.

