### Sample and Recruitment

TBI patients will be recruited through inpatient units at the Affiliated Hospital and the Second Clinical Medical College of North Sichuan Medical University. Recruited participants will be required to present with a clear diagnosis of TBI according to U.S. Centers for Disease Control and Prevention (CDC) guidelines based on clinical and imaging findings. The informed consent process will be carried out by the Principal Investigator. Once participants agree to sign the informed consent form, they will be screened to confirm that they are eligible for study participation according to the following inclusion criteria.

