In the proposed study, resting-state functional magnetic resonance imaging (rs-fMRI) will be used to explore the pathophysiological processes mediating TBI cognitive dysfunction through DLPFC stimulation delivered through rTMS. Disruption of brain network connectivity is an important mechanism leading to cognitive dysfunction in TBI (40); cognitive dysfunction may be primarily associated with disruptions to the default mode network (DMN) (41, 42). The DMN is a task-negative network that is preferentially activated when the individual is not concerned with the external environment and involves several internal cognitions, such as autobiographical memory extraction, looking into the future, envisioning others' perspectives, and processing emotional cognition (43). A recent study found that the DMN is not a single network but rather consists of several intertwined networks. The DMN exhibits positive correlations across internal regions as well as negative correlations with relevant regions of external attentional processing (30). A review of 17 original studies conducted in patients with TBI showed that 53% of these studies reported that rTMS promotes increased brain connectivity, 18% reported that rTMS is associated with decreased functional connectivity, and 29% reported no changes in brain connectivity following rTMS (31). The DLPFC is an important component of the DMN network and its use as a rTMS stimulation site may modulate functional connectivity in the DMN. It is possible that connections within and outside the DMN are transmitted through the paracentral hippocampal cortex and posterior cingulate gyrus as nodes for information transmission (44, 45). As shown by Shang et al. rTMS on the left DLPFC alters the resting-state functional connectivity from the DLPFC to the hippocampal parietal, posterior cingulate cortex (PCC)/precuneus regions in the DMN network (16).

As age, education level, TBI severity, and patients' state of consciousness have been reported as factors influencing patients' cognition (8), this study was proposed to conduct subgroup analyses following measurements of baseline levels of RLAS and MoCA to reduce the effects of raw scores on the obtained results. The rTMS in this study applied to two sites of targeting and may have different efficacy in different subjects, providing a new direction for rTMS intervention in cognition in TBI.

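### The described allocation names no restriction or stratification, so it does not show how 12 per arm is secured and leaves baseline severity to chance in 36 patients

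*Protocol article*

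**What the plan says.** **Allocation.** The Randomization section of the protocol article gives the method in one sentence: "A computer-generated list of random numbers will be placed in an order-numbered, non-transparent, sealed envelope". The same sentence sets the ratio of the three arms at 1:1:1. Study Design repeats that "36 subjects will be randomized in a 1:1:1 ratio". None of these places, nor Interventions, mentions blocking, stratification or minimisation. None says that the list is simple or unrestricted either.

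**Arm size.** Sample Size Estimation arrives at 10 per group, adds 2 for dropout, and concludes: "A total of 12 patients will be allocated to each group".

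**Severity.** The last paragraph of the Discussion lists age, education, TBI severity and state of consciousness as reported influences on cognition. Its response is that "this study was proposed to conduct subgroup analyses following measurements of baseline levels of RLAS and MoCA". Statistical Analysis names ANOVA, or Kruskal-Wallis if the data are not normal, with no covariate. It also says that baseline comparisons ensured the absence of group differences. Table 1 places RLAS and MoCA at screening, before allocation on Day 0.

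**Sites.** The Abstract calls this a "parallel-group, single-center trial". Sample and Recruitment says "TBI patients will be recruited through inpatient units at the Affiliated Hospital and the Second Clinical Medical College of North Sichuan Medical University", and Study Design names the same two institutions.

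**The concern.** A 1:1:1 chance for each patient is not the same as 12/12/12. Equal arms need a restriction on the list, and the article does not name one.

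Severity is the more important part, because it does not depend on how the list was built. A list that forces 12 per arm still does nothing to balance a prognostic factor. The entry criteria leave room for variation: MoCA below 26 with no lower limit, RLAS above VI, and injury at least 6 months earlier. With 12 per arm, a chance gap of several patients in severity can distort the estimated difference in the primary executive outcome. Neither the allocation nor the analysis as stated removes it. Baseline tests can reveal such a gap but cannot prevent it, so the statement that they ensured no differences is not a safeguard.

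**Working it through.** **1. The plan's own figure.** Inputs from Sample Size Estimation: "effect size is 0.7, α is 0.05, power is 0.9". Reading 0.7 as Cohen's f in a one-way ANOVA with three groups, the noncentral F distribution gives power 0.873 at 9 per group and 0.911 at 10 per group. So 10 per group reproduces on that reading. Then 10 + 2 = 12 and 3 × 12 = 36. (The section calls this a non-inferiority calculation, which is a separate matter.) Ten is therefore the number of evaluable patients needed per arm, with room for two losses each.

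**2. Severity when every arm has exactly 12.** The article gives no MoCA distribution, so assume that 18 of the 36 patients are low. The probability of a, b and c low-MoCA patients in the three arms is

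C(12,a) × C(12,b) × C(12,c) / C(36,18), with a + b + c = 18.

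Summing over all splits where the largest and smallest counts differ by 4 or more gives 2,945,720,580 / 9,075,135,300 = 0.325. A gap of 4 out of 12 is 33 percentage points. The dependence on the assumed split is modest:

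| Low-MoCA patients out of 36 | P(gap ≥ 3, i.e. 25 points) | P(gap ≥ 4, i.e. 33 points) |
|---|---|---|
| 18 | 0.53 | 0.32 |
| 12 | 0.49 | 0.28 |

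These figures compare the highest with the lowest of three arms. For one prespecified pair of arms with 18 low, simulation gives 0.31 for 25 points or more and 0.16 for 33 points or more.

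**3. Size of the subgroups.** Statistical Analysis restricts the analyses to completers, so 10 to 12 patients per arm are expected. A split at the middle leaves 10/2 = 5 to 12/2 = 6 per arm in each subgroup.

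**4. Arm sizes if the list were unrestricted (an assumption).** For a multinomial with 36 patients and probability 1/3 for each arm:

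- P(12/12/12) = 36! / (12!³ × 3³⁶) = 0.0226.
- P(at least one arm below 10) = 0.54, before any dropout.
- P(largest minus smallest arm ≥ 6) = 0.49.
- The expected smallest arm is 9.1, and the SD of one arm is √(36 × 1/3 × 2/3) = 2.83.

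**5. What stratified blocks would give.** In each stratum only the last block can be incomplete. An unfinished block of 6 can leave one arm 2 ahead of another, so the gap within a stratum is at most 2. Over two strata the arm totals can differ by at most 2 + 2 = 4. In a simulation of 40,000 lists (block sizes 3 and 6 equally likely, each patient in either stratum with probability 1/2), the totals were equal in 41%, differed by 2 in 55%, and differed by 3 or 4 in about 4%.

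**The case against.** **The list may well be restricted.** The fixed total of 36, the 1:1:1 ratio and the stated 12 per group fit a restricted list better than independent draws, and a journal article commonly leaves block details to the full protocol. This stands. A reader might infer that the trial uses simple randomisation and will miss its arm sizes, but the article does not say so. The figures in step 4 are conditional, and the arm-size part is a request to state the restriction. Even a 9 versus 15 split has an effective size of 2 × 9 × 15 / 24 = 11.25 per arm against 12, so unequal arms alone cost little precision.

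**Chance imbalance is already in the error rate.** Under valid randomisation the test allows for it, the entry criteria narrow severity somewhat, and the Abstract defines the primary outcome as a change. This stands in part. It would be too strong to say that an imbalance will be reported as a treatment effect. But the result of the one trial that is run can still be distorted by a severity gap, and taking change from baseline does not remove a difference in how severe and mild patients change. The article does not merely omit a remedy: it states one, subgroups of a few patients, that cannot do the job.

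**Two hospitals are not proven.** A reader might infer that allocation leaves hospitals unbalanced. The documents do not support this: the Abstract says one center, one ethics committee is named, and one scanner is described. The two names may refer to one institution.

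**Conclusion.** The point holds for severity and, as a matter of wording, for arm size. As described, nothing in allocation or in the stated outcome tests controls a factor that the article itself treats as influencing cognition. On the assumption of an even MoCA split and exactly 12 per arm, the extreme arms differ by a third of their patients in about 32% of randomisations, and in 28% if one third are low. Any such imbalance is a risk and not a certainty. How 12 per arm is secured is unstated, and the 2.3% and 54% apply only if the list is unrestricted. Imbalance by hospital is not established. This should be settled before the first envelope is opened, because allocation cannot be changed afterwards.

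**What to change.** 1. In Randomization, specify computer-generated permuted blocks of varying size (for example 3 and 6), concealed from recruiting and treating staff and stratified by one screening MoCA cut fixed in advance. One factor is enough for 36 patients.
2. In Statistical Analysis, include that factor in the model for the outcomes, and use a stratified rank test if the non-parametric route is taken. Do not rely on RLAS/MoCA subgroups to correct imbalance, and remove the statement that baseline tests ensured no differences.
3. In Sample Size Estimation, write about 12 per arm, since incomplete blocks can leave totals differing by about 2, and rarely by 3 or 4.
4. Reconcile the single-center description in the Abstract with the two institutions in Study Design and Sample and Recruitment. Keep separate lists only if there are two sites.
5. State that whoever prepares the envelopes is also outside recruitment. Blinding already has grouping done by staff outside the intervention.

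The cost is a new list and a few sentences. MoCA is already scored before Day 0, so no new data are needed. The drawbacks are slightly greater predictability at block ends, limited by hiding and varying the block sizes, and a few incomplete blocks. If a restricted list already exists, one sentence settles the arm-size part.
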